## **7.2 Safety Evaluations**

Safety and tolerability of WST-057 will be assessed for the primary objective using the following assessments:

- AEs ([section 7.2.1](#))
- Clinical laboratory tests ([section 7.2.2](#))
- Vital signs ([section 7.2.3](#))
- Physical examination ([section 7.2.4](#))
- Body weight, height, and BMI ([section 7.2.7](#))
- 12-lead ECG ([section 7.2.3](#))
- Concomitant medications ([section 10](#))
- Dermal Draize Score ([section 7.2.5](#))

### **7.2.1 Adverse Events**

The Investigator will determine during the course of all study periods whether any AEs have occurred. The subjects will be questioned in a general way and no specific symptoms will be suggested. Slight flushing and/or a tingling or other altered sensations in the dosing area is expected and is not considered an AE. [Section 11](#) contains additional information with regard to AEs. AEs will be captured from the signing of the informed consent form (ICF).

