## **4 STUDY OBJECTIVES**

### **4.1 Primary Objective**

The primary objective of the study is to determine the safety and tolerability of 2 dose levels of WST-057 (4% pirenzepine free base monohydrate solution) after once-daily topical administration in subjects with type 2 diabetes mellitus (T2DM) with peripheral neuropathy.

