## 4.5 Safety Endpoints

The primary safety endpoints of this study are:

- Adverse events (AE)
- Dermal Draize Score
- Clinical laboratory tests (serum chemistry, hematology, and urinalysis)
- Vital signs
- Body weight
- 12-lead electrocardiogram (ECG)
- Physical examination
- Concomitant medications

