| 
* = It is acceptable to change the schedule of assessments in order to accommodate local and global health concerns and ensure patient safety due to Covid19.
 
a = The ET and EOS visits (week 24) will follow the same procedures.
 
b = Symptom directed physical examination.
 
c = Body weight and BMI calculation only. Height is taken at screening only.
 
d = Blood samples will be collected for serum chemistry and hematology, and urine will be collected for urinalysis (refer to section 7.2.2) at each visit. Subjects will be required to fast for at least 12 hours prior to collection.
 
e = For women of childbearing potential, a serum pregnancy test will be performed at screening and EOS/week 24. A urine pregnancy test will be performed at the Baseline visit.
 
f = Two standard 3-mm skin biopsies will be collected during the Screening visit from the distal leg or calf; approximately 10 cm above the malleolus and 3 cm to the posterior; and from the untreated area on the lateral thigh, approximately 25 cm below the iliac spine, approximately 5 cm below the level of the pubis and 8 cm to the posterior.
 
g = Prophylactic antibiotics may be administered to participants who, in the judgment of the Investigator, are considered to be at high risk for infection of the biopsy site.
 
h = Randomization will be prior to dose administration on day 1.
 
i = Investigational product will be administered by the subject by dispensing material from pump into palms of the hand and then spreading evenly over the calves (mid-calf sock-line), ankles and tops, and bottoms of feet.
 
j = Skin irritation (including dryness, redness, swelling, itching, burning/stinging) at the application site will be assessed using a Dermal Draize Scale prior to dosing on visit days.
 
k = Trough blood samples (1 sample at each specified visit) will be collected for pharmacokinetic analysis.
 
l = Two standard 3-mm skin biopsies will be collected during the EOS visit for early terminations or the week 24 visit. The biopsies will be collected at a distance of no less than 2 cm away and no further away than 3.5 cm from the baseline biopsy location.
 
m = The biopsy sites will be examined at the 26-week visit to monitor healing and remove sutures, if necessary. If the sutures are not suitable for removal, another visit for suture removal will be scheduled.
 
n = The visual analogue score will be collected weekly via a mobile phone application completed by the patient at the same time each week.
 |                |                |            |                |                  |                |                |                |                |                       |                 |

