#### **7.2.5 Local Skin Irritation Assessment (Dermal Draize Score)**

No local skin irritation is expected to be observed based on nonclinical studies of primary dermal toxicity and a dermal sensitization. However, as noted in the physician's insert for Gastrozepin (50 mg oral pirenzepine), a flushing or slight redness may occur at the test site.

The application site will be monitored for signs of irritation, including dryness, redness, swelling, and itching/burning. The Dermal Draize Scale will be used for recording of skin reactions ([Appendix A](#)).

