## 11 ADVERSE EVENTS

### 11.1 Adverse Event Definition

An AE is any untoward medical occurrence in a subject administered a pharmaceutical product, which does not necessarily have to have a causal relationship with the pharmaceutical product treatment. An AE can, therefore, be any unfavorable and unintended sign, symptom, or disease temporally associated with the use of a medicinal product, whether or not related to the medicinal product. Any worsening of the subject's disease under study or other medical conditions will also be considered to be an AE, unless it is within the normal range of disease fluctuation for that subject.

Clinically meaningful (for a given subject) changes in physical examination findings and abnormal objective test findings (eg, laboratory, X-ray, or ECG) should also be recorded as AEs. The criteria for determining whether an abnormal objective test finding should be reported as an AE are as follows:

1. Test result is associated with accompanying symptoms or is of clinical concern.
2. Test result requires additional diagnostic testing or medical/surgical intervention.
3. Test result leads to a change in study dosing or discontinuation from the study, significant additional concomitant drug treatment, or other therapy.
4. Test result leads to any of the outcomes included in the definition of an SAE.

Note that merely repeating an abnormal test, in the absence of any of the above conditions, does not meet condition 2 above for reporting as an AE.

Any abnormal test result that is determined to be an error does not require reporting as an AE.

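### Section 7.2.1 takes tingling and other altered sensations in the dosing area out of AE reporting, in conflict with Section 11.1, and the Dermal Draize Score fills the gap only in part

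*Protocol*

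**What the plan says.** Section 4.1 gives the aim: "The primary objective of the study is to determine the safety and tolerability of 2 dose levels of WST-057". Section 4.5 then lists eight primary safety endpoints. Adverse events are one, and "Dermal Draize Score" is another.

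Four places govern what is recorded about the treated skin.

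- **Section 7.2.1** tells the investigator: "Slight flushing and/or a tingling or other altered sensations in the dosing area is expected and is not considered an AE". It also says that subjects are questioned in general terms, without naming symptoms. It points to Section 11 only for additional information.
- **Section 11.1** defines an AE as any unfavorable and unintended sign, symptom or disease associated in time with the product, related or not. Worsening of the "disease under study or other medical conditions will also be considered to be an AE", unless it lies within that subject's normal fluctuation.
- **Section 7.2.5** says "No local skin irritation is expected to be observed based on nonclinical studies". Its next sentence allows that flushing or slight redness may occur at the site, citing the oral product's insert.
- **Table 1, footnote j (Section 5.3)** says that skin irritation "will be assessed using a Dermal Draize Scale prior to dosing on visit days".

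Section 13.1.4 summarizes AEs by body system and preferred term, and by number, intensity and relationship per treatment group. It also counts the AEs that lead to withdrawal.

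**The concern.** The sentence in 7.2.1 excludes events because they are expected. Section 11.1 has no exemption for expected events, and nothing says which section prevails. One site may enter a bothersome tingling as an AE while another, following 7.2.1, does not.

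The exclusion is also open-ended. The word slight attaches to flushing. It does not clearly limit tingling, and it does not limit other altered sensations in intensity or duration.

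Altered sensation in the feet is moreover a symptom of the disease under study: Section 3.1 names paresthesia, dysesthesias and neuropathic pain as results of small fiber disease. The dosing area (calves, ankles, feet) lies in the lower extremities, where inclusion criterion 3 requires the neuropathy to be. A new or worse dysesthesia there can be an AE under 11.1 and not an AE under 7.2.1.

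At stake is the AE part of the primary assessment. An event never entered in the eCRF cannot be restored by any analysis plan.

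**Working it through.** The protocol states no event rate, power or error level for the safety endpoints, so there is no figure to reproduce. The check is a comparison of rules and one count.

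**Step 1: what each rule captures.** The Draize column uses the five items of Appendix A: dryness, erythema, pruritus, burning/stinging and edema.

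| Event in the dosing area | AE under 11.1 | AE under 7.2.1 | Draize item |
|---|---|---|---|
| Slight flushing or redness | Yes, if unfavorable and unintended | No | Yes (erythema) |
| Burning or stinging | Same | No, if read as an altered sensation | Yes |
| Itching | Same | Unclear | Yes (pruritus) |
| Tingling | Same | No | None |
| Numbness or other altered sensation | Same | No, at any intensity | None |
| Worse paresthesia or dysesthesia from the neuropathy | Yes, if beyond normal fluctuation | No, on a plain reading | None |

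For the last three rows, a site that follows 7.2.1 records the event neither as an AE nor on the Draize scale.

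**Step 2: how often the Draize scale is read.**

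- Daily applications over 24 weeks (Section 5.1): 24 × 7 = 168.
- On-treatment readings, at weeks 2, 4, 8, 12, 16, 20 and 24 (Section 5.1): 7.
- Share of application days with a reading: 7 / 168 = 4.2%.
- Spacing of readings: 2 weeks up to week 4, then 4 weeks.

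**Step 3: how long after an application it is read.** Footnote j puts the reading before that day's dose, and Section 9.5 asks for application at about the same time each day. The previous application is then up to about 24 hours old. Section 9.5 gives evening use as its example. Assuming application at 20:00 and a visit between 08:00 and 16:00, the reading falls 12 to 20 hours later. The visit hours are my assumption; the protocol gives none. Redness or burning that fades within hours may be gone by then.

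**Step 4: what reaches the tables.** The AE summaries in Section 13.1.4 use recorded AEs only. An excluded reaction is absent from incidence, intensity, relatedness and AE-related withdrawal. Section 12.4 wants a withdrawal due to an AE recorded against a specific AE. A subject who stops because of tingling has no such AE under 7.2.1. The Draize scale grades severity but carries no relationship, action taken or outcome.

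**The case against.** The strongest reply is that local tolerability is not lost. The Dermal Draize Score stands beside AEs in Section 4.5. It grades redness, itching and burning or stinging from barely noticeable upward, at screening, baseline and all seven on-treatment visits. Its pruritus grades include occasional itching and itching that disturbs sleep, which must rest partly on recall. A physical examination with dermatological and neurological parts takes place at each treatment visit. This stands. A reader might infer from 7.2.1 that the expected drug reactions vanish from the primary safety assessment altogether. The protocol does not support that: they leave AE reporting, and Draize keeps part of them.

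A reader might also infer that the AE comparison is biased towards no difference because the excluded events fall mainly in the active arms. That is unproven. At equal volume, Table 3 gives placebo the same dimethyl sulfoxide (292.6 mg at 2 mL) and ethanol (740.8 mg), and subjects in every arm have a disease that causes paresthesia. Section 7.2.5 links only flushing or redness to pirenzepine.

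Nor do 7.2.1 and 7.2.5 contradict each other outright, because 7.2.5 goes on to allow flushing or slight redness. The mismatch lies in one section expecting sensations and the other expecting no irritation.

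Last, worsening neuropathy would not go unobserved. The Toronto scores and the Norfolk-QOL-DN are taken at each treatment visit and the pain VAS weekly. But Section 4.4 lists these as pharmacodynamic endpoints; they do not feed the AE tables. Section 11.1 would make such worsening an AE, and 7.2.1 gives a site a written reason not to record it.

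**Conclusion.** The concern holds in a limited form. Section 7.2.1 conflicts with 11.1 on what counts as an AE in the treated area. Tingling, numbness and other altered sensations there are covered neither by AE reporting under 7.2.1 nor by any Draize item. Redness and burning or stinging are covered only in so far as they are found at 7 pre-dose readings, on 4.2% of application days. AE incidence, intensity, relatedness and AE-related withdrawal by arm will understate local reactions, and sensory worsening can be left out of AE reporting.

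The number of events lost cannot be estimated, because the protocol gives no rate for such reactions. The direction of any active-placebo bias is not established. No sample size or error rate is affected. The conclusion assumes that sites apply 7.2.1 as written, and that at least some excluded reactions are unfavorable and unintended and so meet 11.1.

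**What to change.** - Delete the exclusion sentence in Section 7.2.1 so that 11.1 governs.
- Reconcile what 7.2.1 and 7.2.5 say is expected at the application site.
- Record local reactions that meet 11.1 as AEs, with intensity and relationship.
- Tabulate application-site reactions by arm next to the Draize results.

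The cost is one deleted sentence, an edit to 7.2.5, a memo to sites and one table. The downside is more mild AEs. The change should be made while data are still being collected, since unrecorded events cannot be reliably recovered.

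Symptom-specific AE questions at visits are not needed for this fix. They would conflict with the rule in 7.2.1 and 11.2 that no specific symptoms are suggested, and should not be added unless that rule is reconciled too.

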### **7.2.2 Clinical Laboratory Tests**

Clinical laboratory tests will be performed by a qualified laboratory. Blood and urine samples will be taken prior to the dosing (on dosing days) at the clinic visits indicated for clinical chemistry, hematological analysis, and urinalysis. Subjects should be fasted prior to the collection of samples (12 hours prior to sample collection).

The following parameters will be measured:

|                                  |                                                                                                                                                                                                                                                                                                                                                              |
|----------------------------------|--------------------------------------------------------------------------------------------------------------------------------------------------------------------------------------------------------------------------------------------------------------------------------------------------------------------------------------------------------------|
| Hematology:                      | Hematocrit, hemoglobin, red blood cell (RBC) count, white blood cell (WBC) count, differentials (neutrophils, eosinophils, basophils, lymphocytes, and monocytes), platelet count, and reticulocytes                                                                                                                                                         |
| Clinical Chemistry:
(Chem 20) | Albumin, alkaline phosphatase, ALT, AST, blood urea nitrogen, calcium, chloride, CO 2 , creatinine, direct bilirubin, gamma-glutamyl transferase, glucose, lactate dehydrogenase, phosphorus, potassium, sodium, total bilirubin, total cholesterol (triglycerides and HDL/LDL cholesterol including total cholesterol), total protein, uric acid |
| Urinalysis:                      | Color, specific gravity, pH, glucose, ketones, protein, bilirubin, urobilinogen, WBCs, RBCs, and microscopy                                                                                                                                                                                                                                                  |

For females of childbearing potential, a serum pregnancy test will be performed at screening and at the end of study/week 24 visit, and a urine pregnancy test at baseline.

Serology for hepatitis B surface antigen, hepatitis C antibody, and HIV 1 and 2 antibody will be conducted at screening and baseline to confirm eligibility.

A urine drug screen will be performed at screening and baseline. Urine samples will be collected in a container labeled "URINE DRUG SCREEN".

Study site SOPs for requesting and documenting clinical laboratory samples will be followed for this study.

Laboratory reports should be reviewed, signed, and dated by the Investigator or delegated physician. Each abnormal result will be assessed as clinically or not-clinically significant and a comment will be provided for all out-of-range analytes deemed clinically significant (ie, document probable cause for abnormal results). Laboratory data will be collected electronically and transferred to the contract research organization (CRO) handling the case report form data for integration with the eCRF data.

### **7.2.3 ECG and Vital Signs**

A 12-lead ECG will be obtained at the visits indicated in Schedule of Assessments and will include ventricular rate (beats per minute [bpm]), PR, QRS, QT, QTc, QTcF, and QTcB interval measurements and calculations.

The 12-lead ECGs will be digitally recorded after 10 minutes rest in the sitting position. All ECGs will be over-read by an appropriately qualified clinical staff physician and the data entered in the subject's CRF or via validated direct electronic transfer for integration with the eCRF data.

ECG findings will be classified as normal or abnormal and associated interpretive remarks will be captured. The clinical significance of ECG findings will be determined by the Investigator after review of the ECG report with relation to the subject's medical history, physical examination, and concomitant medications.

Vital signs (BP [mmHg], respiratory rate [breaths per minute], temperature [°F], and heart rate [bpm]) will be measured at the clinic visits or time points indicated in the Schedule of Assessments. Blood pressure will be measured after at least a 5-minute rest in the sitting position. Blood pressure will be measured with a standard mercury sphygmomanometer or an automated oscillometric BP monitor.

#### **7.2.4 Physical Examination**

A physical examination will be performed at the time points indicated in the Schedule of Assessments. This evaluation will include examination of the following body systems: general appearance; eyes, ears, nose, and throat; head and neck; chest and lungs; cardiovascular; abdomen; musculoskeletal; lymphatic (head and neck); dermatological (including the palms of hands to evaluate any investigational product reaction); neurological; and extremities. Urogenital and psychiatric abnormalities will be accessed as part of the subject's medical history at screening, and any abnormalities (ie, if the subject has a complaint for that system) in these systems during the treatment period will be recorded as AEs.

The physical examination at the follow-up visit (week 26) will be a symptom directed examination.

#### **7.2.5 Local Skin Irritation Assessment (Dermal Draize Score)**

No local skin irritation is expected to be observed based on nonclinical studies of primary dermal toxicity and a dermal sensitization. However, as noted in the physician's insert for Gastrozepin (50 mg oral pirenzepine), a flushing or slight redness may occur at the test site.

The application site will be monitored for signs of irritation, including dryness, redness, swelling, and itching/burning. The Dermal Draize Scale will be used for recording of skin reactions ([Appendix A](#)).

#### **7.2.6 Demographics and Medical History**

Demographics and brief, relevant medical and social history will be taken at screening, including tobacco use and alcohol consumption.

#### **7.2.7 Body Weight, Height, and Body Mass Index**

Body weight and height (screening only) will be measured at the time points indicated in the Schedule of Assessments. BMI will be calculated and used to confirm eligibility using body weight from the screening visit and height from the screening visit, using the following formula:

$$\frac{\text{weight(kg)}}{\text{height}^2(\text{m}^2)} \quad \text{OR} \quad \frac{\text{weight(pounds)} \times 703}{\text{height}^2(\text{inch}^2)}$$

### 7.3 Pharmacokinetic Evaluations

Trough blood samples will be collected at the time points indicated in the Schedule of Assessments. The concentration of pirenzepine in these samples will be analyzed by a contract bioanalytical laboratory using a validated liquid chromatography coupled to tandem mass spectrometry (LC/MS-MS) method. Full details of the methodology will be presented in the bioanalytical report, which will be appended to the clinical study report. The data obtained from these analyses may be used to calculate the following pharmacokinetic parameters: minimum plasma concentration ( $C_{min}$ ), elimination rate constant ( $\lambda_z$ ), half-life ( $t_{1/2}$ ), apparent clearance ( $CL/F$ ), and apparent volume of distribution ( $V_z/F$ ).

### 7.4 Data Monitoring Committee

A formal data monitoring committee is not planned for this study.

### 7.5 Total Blood Volume

The total volume of blood obtained from an individual study participant is expected to be approximately 105 mL, including PK samples (14 mL) and clinical laboratory tests (91 mL).

### 7.6 Pharmacokinetic Sampling

Samples of venous blood will be obtained in dipotassium ethylenediaminetetraacetic acid (K2EDTA) tubes (a minimum of 2 mL per time point required) at the time points indicated in the Schedule of Assessments.

Immediately after collection, the tube will be gently inverted several times to mix the anticoagulant with the blood sample. The plasma fraction will be separated by placing the collection tube into a refrigerated centrifuge (4°C to 8°C) for 10 minutes at approximately  $1500 \times g$ . The plasma fraction will be withdrawn by pipette and divided into 2 polypropylene freezing tubes (designated primary and secondary samples), with each tube receiving approximately equal aliquots. All sample collection and freezing tubes will be clearly labeled in a fashion that identifies the subject, the study period, and the collection time. Labels will be fixed to freezing tubes in a manner that will prevent the label from detaching after freezing. All plasma samples will be processed and placed into a freezer ( $< -20^\circ\text{C}$ ) within 1 hour after collection.

All plasma samples will be stored frozen ( $< -20^\circ\text{C}$ ) until they are shipped to the analytical facility. Prior to shipping, the samples will be packed into thermal insulated containers and packed in sufficient dry ice to assure that they remain frozen for a minimum of 72 hours and protected from breakage during shipment, and will be accompanied by an Excel spreadsheet manifest detailing the contents of each shipment. The bioanalytical facility will be notified of the shipment via e-mail or facsimile. Samples will be shipped by overnight priority courier. The samples will be divided into 2 shipments, each containing 1 aliquot of plasma for each time point. After receipt of verification that the first shipment was received by the analytical facility, the second shipment will be sent. On the day of shipment, the site will e-mail notice to the laboratory and sponsor with the tracking number and a copy of the shipping manifest.

All samples will be shipped to:

